## Secondary Objectives

1. To assess and compare the duration of specific antibody response over an 18 month period.
2. To measure the effect of boosting at 4 months on specific antibody levels.

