## Cohort Allocation

Volunteers will be randomized to one of six vaccine cohorts. Within each vaccine cohort, 2 volunteers will be randomized to receive placebo, and 10 volunteers to receive vaccine.

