## Clinical Monitoring and Evaluation

See **Appendix D** for a tabular representation of study procedures. In addition to the procedures listed below, photographs of the injection may be taken at baseline and on follow-up visits to better assess and evaluate local reactogenicity.

Study Day 0 (Day of First Vaccination)

1. Verify that Informed Consent was obtained.
2. Verify that all applicable eligibility criteria have been met.
3. Perform abbreviated history and physical exam, focusing on any acute complaints.
4. Obtain approximately 35 mL of blood for hematology, biochemistry, antibody ELISA and membrane feed assay.
5. For females, obtain a urine sample for -hCG testing. Ensure that test is negative before vaccinating; a positive test will exclude the volunteer from the trial.
6. Record vital signs (blood pressure, temperature, heart rate, and respiratory rate).
7. Administer the vaccine.
8. Observe for at least 30 minutes after vaccination to evaluate for immediate adverse reactions.
9. Education by study staff during 30-minute post-immunization wait period describing proper use of digital thermometers, injection-site reaction measurement and malaria vaccine side-effect diaries. Study staff will also discuss signs and symptoms of potential adverse events (AEs).
10. Distribute Days 0-6 diary card.

Study Day 1

1. Perform basic history and physical exam (including injection site), emphasizing examination of any acute complaints.
2. Record vital signs.

Study Day 3

1. Perform basic history and physical exam (including injection site), emphasizing examination of any acute complaints.
2. Record vital signs.
3. Obtain approximately 10 mL of blood for hematology and biochemistry tests.

Study Day 7 +/- 1

1. Perform basic history and physical exam (including injection site), emphasizing examination of any acute complaints.
2. Record vital signs.
3. Collect Days 0-6 diary card.
4. Draw approximately 3.5 mL of blood for CBC and differential
5. Distribute Days 7-13 diary card.

Study Day 14 +/- 2

1. Perform basic history and physical exam (including injection site), emphasizing examination of any acute complaints.
2. Record vital signs.
3. Obtain approximately 15 mL of blood for hematology, biochemistry, and antibody ELISA.
4. Collect Days 7-13 diary card.
5. Distribute Days 14 – 20 diary card.

Study Day 21 +/- 2

1. Perform basic history and physical exam (including injection site), emphasizing examination of any acute complaints.
2. Record vital signs.

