3. Collect Days 14 – 20 diary card.

Study Day 30 +/- 7(1 month after first vaccination)

1. Perform basic history and physical exam (including injection site), emphasizing examination of any acute complaints.
2. Record vital signs.
3. Obtain approximately 5 mL of blood for antibody ELISA.

Study Day 60 +/- 7 (2 months after first vaccination)

1. Perform basic history and physical exam (including injection site), emphasizing examination of any acute complaints.
2. Record vital signs.
3. Obtain approximately 35 mL of blood for hematology biochemistry, antibody ELISA & membrane feeding assay.

Study Day 90 +/- 7 (3 months after first vaccination)

1. Perform basic history and physical exam (including injection site), emphasizing examination of any acute complaints.
2. Record vital signs.
3. Obtain approximately 5 mL of blood for antibody ELISA.

Study Day 120 +/- 7 (Day of Second Vaccination)

1. Perform basic history and physical exam (including injection site), emphasizing examination of any acute complaints.
2. Obtain approximately 35 mL of blood for hematology, biochemistry, antibody ELISA, and membrane feeding assay
3. For females, obtain a urine sample for -hCG testing. Ensure that test is negative before vaccinating; a positive test will exclude the volunteer from the trial.
4. Record vital signs (blood pressure, temperature, heart rate and respiratory rate).
5. Administer the vaccine.
6. Observe for at least 30 minutes after vaccination to evaluate for immediate adverse reactions.
7. Education by study staff during 30-minute post-immunization wait period describing proper use of digital thermometers, injection-site reaction measurement tools and patient diaries. Study staff will also discuss signs and symptoms of potential AEs.
8. Distribute Days 0-6 diary card.

Study Day 121 (1 day after Second Vaccination)

1. Perform basic history and physical exam (including injection site), emphasizing examination of any acute complaints.
2. Record vital signs.

Study Day 123 (3 days after Second Vaccination)

1. Perform basic history and physical exam (including injection site), emphasizing examination of any acute complaints.
2. Record vital signs.
3. Obtain approximately 10 mL of blood for hematology and biochemistry tests.

Study Day 127 +/- 1 (7 days after Second Vaccination)

1. Perform basic history and physical exam (including injection site), emphasizing examination of any acute complaints.
2. Record vital signs.
3. Collect Days 0-6 diary card.

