4. The proportion of volunteers with at least one local adverse event will be compared by dose cohort for each vaccine.  Formal statistical tests will assess whether the three cohorts differ with respect to these proportions, and whether there is a dose-response relationship. To see if there is a difference in adverse events between the initial vaccination and the subsequent vaccination we perform a sign test, where the response for each volunteer is the difference between the number of adverse events in the 60 days following the first vaccination and the number of adverse events in the 60 days following the second vaccination.
5. To determine the dose that generates the highest serum antibody levels to homologous antigen at Day 150 (1 month after the second immunization).

 i.   A Kruskal-Wallis test will be performed to check for any significant differences in the antibody concentrations of the three dose groups.  If that test is significant, then all three pairwise Mann-Whitney tests will be performed to see which pairs have significant differences. If the Kruskal-Wallis test is not significant then we will not perform any Mann-Whitney tests on the pairs of dose groups.  All of the tests can be performed at the 0.05 level and they will retain a family-wise error rate of 0.05

Secondary Objective 1: To assess and compare the duration of specific antibody response to homologous Pfs25 or Pvs25 over an 18 month period.

1. Describe immunogenicity responses by vaccine and dose group, over time.
2. Individual responses will be described over time and stratified by dose cohort.
3. Antibody concentration will be measured at Days 0, 14, 30, 60, 90, 120, 134, 150, 180, 270, 360 and 556. To exploit the multiple measures of antibody within each subject, a longitudinal model will be built to describe the antibody response over time. The model will explore if there are any differences between Pfs25 and Pvs25 and explore dose effects.

Secondary Objective 2: Measure the effect of boosting at 4 months on antibody units.

1. Using difference in antibody level from Day 0 to Day 150 as the response, exact Jonckheere-Terpstra tests will be performed to determine if there is a dose response. Using the same response, exact stratified Wilcoxon rank sum tests, stratified on dose level, will be performed to determine if there are differences between the dose groups. If feasible, similar tests may be done using the longitudinal model described above.

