2. In addition, the increase in the levels of antibody between Day 120 and Day 150 will be estimated and compared.
3. Waning will be assessed by comparing levels of antibody at Days 180, 270, 360 and 556 with the level at Day 150.

The following tertiary objectives are for information only:

Tertiary Objective 1: To measure the ability of the vaccine induced antibody to significantly reduce or block oocyst development in the mosquito as measured by the membrane feeding assay for both Pvs25 and Pfs25.

1. Graphs will display growth inhibition (the ability of the antibody to significantly reduce or block oocyst development) expressed as a percent of inhibition comparing test sera to pre-immune sera.
2. Depending on the distribution of the data, parametric or non-parametric methods will be used to compare inhibition as a function of dose, and serotype.

Tertiary Objective 2: To determine the relationship between antibody levels and degree of in vitro oocyst development.

Non-linear regression will be used to model growth inhibition and the ELISA value giving 50% growth inhibition will be estimated.

Should the need arise for terminating the study early, the investigative team will discuss with the SMC the reason for termination and determine which study questions can be addressed in an unbiased manner with the available data. The available data will be analyzed and interpreted in light of early termination. Deviations from the statistical plan will be reported in the study report.

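### The tests named for the effect of boosting use the Day 0 to Day 150 change, which combines the response to dose 1 with the response to the boost

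*Protocol*

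**What the plan says.** Protocol section 2.2 gives Secondary Objective 2 as "To measure the effect of boosting at 4 months on specific antibody levels". Section 6.5 and Appendix D place the first vaccination on Day 0 and the second on Day 120 (window 7 days either way). An ELISA sample is taken at the Day 120 visit, and section 6.5 lists that blood draw ahead of the injection.

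Section 9.1.1 lists three items under this objective.

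- Item 1 holds the only named tests. For dose response: "Using difference in antibody level from Day 0 to Day 150 as the response, exact Jonckheere-Terpstra tests will be performed". Then: "Using the same response, exact stratified Wilcoxon rank sum tests, stratified on dose level, will be performed", with the stated aim of finding differences between the dose groups. Similar tests in the longitudinal model are optional.
- Item 2 adds that "the increase in the levels of antibody between Day 120 and Day 150 will be estimated and compared". It names no test, scale or groups to be compared.
- Item 3 assesses waning against Day 150.

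The samples for a boost-specific analysis exist: "Antibody concentration will be measured at Days 0, 14, 30, 60, 90, 120, 134, 150, 180, 270, 360 and 556". In each cohort, section 3.3 says, "2 volunteers will be randomized to receive placebo, and 10 volunteers to receive vaccine". The immunization schedule in the Protocol Summary gives each volunteer the same product at both visits, so no arm is primed and left unboosted.

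**The concern.** The effect of an injection given on Day 120 is what happens after Day 120. A change measured from Day 0 also contains whatever remains of the response to the first injection. A dose effect on priming can then be read as a dose effect on boosting, and a dose effect on boosting can be cancelled by an opposite one on priming.

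Section 1.5 describes the volunteers as malaria-naive, although section 4.2 does not exclude past malaria. If Day 0 levels are near background, Day 150 minus Day 0 is almost the Day 150 level, which is already compared across doses under the primary objective. Item 1 would then add little about boosting.

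Section 9.1 says the results will inform dosing and scheduling in later trials. Whether the second injection adds anything, and at which dose, bears directly on scheduling.

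**Working it through.** The plan gives no figure for this point, so there is none to reproduce.

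**Decomposition.** With D*t* the antibody level on Day *t*:

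D150 − D0 = (D120 − D0) + (D150 − D120)

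The first bracket is the response to dose 1 still present on Day 120. The second is the change after the boost. Item 1 tests the sum.

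**Example with no boost effect.** Take baseline 1 and Day 120 medians of 10, 22.4 and 50 (a 5-fold gradient, equal steps of √5). If Day 150 equals Day 120, the item 1 response is about 9, 21.4 and 49, a clear dose trend. D150/D120 is 1 at every dose.

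**Inputs from the protocol.** Three doses per antigen and 10 vaccinees per dose (section 3.3). Coefficient of variation 1.2 to 1.4 and a five-fold difference as the effect size of interest (section 9.2). For a lognormal variable, log-SD = √ln(1 + CV²):

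- CV 1.2: √ln 2.44 = 0.94
- CV 1.4: √ln 2.96 = 1.04

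Log-SDs of 1.2 to 1.4 were added as stress values.

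**Assumptions not in the protocol.** Lognormal levels; lowest-dose Day 120 median ten times baseline; log-SD 0.3 for baseline and for the within-person noise from Day 120 to Day 150; two-sided alpha 0.05. The test is Jonckheere-Terpstra with a simulated permutation null (attained size about 0.049).

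**No boost effect, 5-fold priming gradient: share of trials rejecting**

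| Between-person log-SD | D150 − D0 | D150 − D120 | log(D150/D120) |
| --- | --- | --- | --- |
| 0.94 | 92% | 7% | 5% |
| 1.04 | 87% | 6% | 5% |
| 1.2 | 78% | 6% | 5% |
| 1.3 | 70–72% | about 6% | about 5% |
| 1.4 | 65% | 6% | 5% |

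**Equal priming, no boost effect.** All three responses reject in about 5%.

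**Opposite gradients.** With priming 1:3:9 and boost ratio 9:3:1, the products are 9:9:9. D150 − D0 rejects in about 5%, the raw D150 − D120 change in 90 to 96%, and the log ratio in 100%. A strongly dose-dependent boost is invisible to item 1.

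**Equal priming, same 5-fold boost at every dose.** All three responses reject in about 5%, although the boost works. A trend test across doses cannot show whether boosting raises antibody.

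**Power when only the boost varies by dose.** Suppose noise of log-SD *w* enters each visit separately and the between-person log-SD is *b*. The log ratio has SD *w*√2. The log Day 150 level has SD √(*b*² + *w*²). The ratio is the less variable when 2*w*² < *b*² + *w*², that is, when *w* < *b*. With *b* = 0.9 and a boost rising from 4- to 12-fold, runs gave these powers:

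- *w* = 0.3: 68–77% for D150 − D0, 100% for the ratio
- *w* = 0.7: 52–59% against 65%
- *w* = 0.9: 44–47% against 43–44%

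**The case against.** The best defence is item 2. The Day 120 to Day 150 increase is planned under the same objective, and section 9.1.1 promises estimates with 95% confidence intervals. It also says that a detailed analytic plan will fully describe the methods, so the missing test and scale in item 2 are no fault in a protocol. This stands: a reader might infer that the boost contrast was overlooked, and the text does not support that.

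Item 1 also says only that it looks for a dose response. As a statement about the two-dose change, a significant result would be correct. That stands too, but item 1 is filed under the boosting objective and holds its only named tests, so its result invites the wrong reading.

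A reader might go further and say that the raw Day 120 to Day 150 difference is equally contaminated. With the same 4-fold boost at every dose and a 5-fold priming gradient it does reject in 71 to 91%, against about 5% for the ratio. But the absolute increments then truly differ by dose, so this is a choice of scale. With no boost effect the raw difference rejects in only about 6 to 7% under the 5-fold gradient.

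Nor can a large gain in power be promised. It depends on within-person noise, which the protocol does not give, and disappears when that noise is as large as the spread between persons.

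**Conclusion.** The point holds as a mismatch between a stated response and its objective. Item 1 tests priming and boosting together. With a 5-fold priming gradient and no boost effect, the Jonckheere-Terpstra test rejects in about 70 to 92% of trials for between-person log-SD 0.94 to 1.3, and it can miss a dose effect on boosting that runs against the priming gradient. These figures rest on the lognormal model, the within-person log-SD of 0.3 and the assumed gradient. If priming does not differ by dose, the test keeps its 5% when the boost does nothing.

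This should be fixed, but it does not undermine the trial. The objective is secondary, the right window is already planned in item 2, and no decision rule uses the item 1 p-value. The interim report in section 8.2 rests on the serologic response one month after the second injection.

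Two limits remain under any response. A trend test across doses does not show that boosting works. And with no primed but unboosted arm, the Day 120 to Day 150 change is a before-and-after estimate.

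The stated purpose of the Wilcoxon test is a separate wording error: a test stratified on dose cannot detect differences between dose groups.

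**What to change.** In section 9.1.1, Secondary Objective 2:

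1. Make the Day 120 to Day 150 change the named response, preferably log(Day 150/Day 120).
2. For each vaccine and dose, report the geometric mean ratio with its 95% CI and a within-person paired test. This answers whether antibody rises after the boost.
3. Apply the exact Jonckheere-Terpstra test to that ratio for dose trend.
4. Keep the Day 0 to Day 150 tests, relabelled as the overall two-dose response.
5. State what the dose-stratified Wilcoxon test compares. It may be meant for the two vaccines, but the text says dose groups, so the authors must settle this.

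The cost is wording only, since both samples are already scheduled. There are two small downsides. Day 120 values below the assay limit need a stated floor before a ratio is taken, and volunteers who do not receive dose 2 drop out of this analysis.

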## Immunologic Testing

### Antibody Assay (ELISA)

Serum antibody levels to the Pfs25 and Pvs25 antigens will be measured by ELISA. Briefly, microwell plates (Dynex Technologies) are coated overnight at 4oC with 100 μL/well of antigen solution (1 μg/mL). Plates are washed with TRIS-buffered saline (TBS) containing 0.1% Tween‑20 (0.1% T-TBS) and blocked with TBS containing 5% skim milk powder for 2 hours at room temperature. After washing with 0.1% T-TBS, serum samples at a dilution of 1:5,000 in 0.5% T-TBS containing 5% skim milk powder are added in triplicate and incubated for 2 hours at room temperature. After incubation, unbound antibodies are removed by washing the plates with 0.1% T-TBS, and 100 μL of alkaline phosphatase-conjugated goat anti-human IgG solution (Kirkegaard & Perry Labs, Gaithersburg, Maryland, 1:1,000 dilution in 0.5% T-TBS containing 5% skim milk powder,) is added to each well and incubated for 2 hours at room temperature. Plates are then washed with 0.1% T-TBS, followed by adding 100 μL of phosphatase solution (Sigma, St. Louis, Missouri) to each well; the plates are then covered with aluminum foil and incubated for 20 minutes at room temperature for color development. The plates are read immediately at 405 nm with a microplate reader (Spectramax 340PC Molecular Devices). The optical density values are used to determine anti-Pfs25 and anti-Pvs25 antibody concentration by comparison to a standard curve generated with known positive control sera included on each ELISA plate.

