### Description of the Statistical Methods to Be Employed

The purpose of this trial is to estimate event rates and patterns of immune responses as well as to compare these rates and patterns in different doses of the study vaccines and to compare the response by the two vaccines. This section briefly describes the statistical methods to be used. A detailed analytic plan will fully describe the methods. The analytic plan will discuss the planned approaches to missing data. Listings will show all observed data and, if applicable, impute values and the approaches taken for imputation.

Estimates will be presented with their 95% confidence intervals. Descriptive approaches will be used to meet the protocol objectives as stated in **Section** **2.0** of this protocol. In particular, the immunologic response for each of the 72 volunteers will be presented as individual graphs,

and all adverse events will be listed. Formal statistical tests, as outlined below, will be used to compare doses.

Statistical tests on the adverse event data will be performed without correction for multiplicity, because typically the family-wise Type I error is not bound for tests of safety. A nominal Type I error rate of 10 percent will be used. Most of the analyses of immunogenicity will be based on a longitudinal mixed model with terms for dose group for each of the 2 vaccines.

Primary Objective: To assess the safety, reactogenicity, and immunogenicity of the PpPfs25/ISA51 and ScPvs25/ISA51 malaria vaccines.

1. Summarize the frequency of immediate, systemic and local AEs.
2. Line listing of individual clinical and laboratory AEs as classified by immediate (within the first 30 minutes), systemic and local will be displayed in tabular format and stratified by dose cohort.
3. AEs will be summarized by severity and relationship to vaccine by individuals and dose cohort.

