## Sample Size

Based on an analysis of the human antibody responses to a number of malaria antigens that have been tested in clinical trials (the three components of Combination B [6] and RTS,S [7]), the observed coefficient of variation in the range of antibody concentrations has been found to be remarkably constant at approximately 1.2 - 1.4. Based on the distribution of antibody responses for each of the antigens in the combination B and RTS,S trials, a sample size of 10 volunteers per dose group would permit detection of at least a five-fold difference in antibody concentration between groups using a Mann-Whitney test, assuming a level of significance of 0.05 and a power of 0.80. Additionally, a group size of 10 volunteers per dose gives 0.80 probability for detecting one or more serious or severe AE that occurred with a probability of 0.15 per volunteer.

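### The Wilcoxon test stratified on dose level (Secondary Objective 2) cannot show whether the dose groups differ; the sentence must say which comparison is meant

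*Protocol*

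**What the plan says.** Protocol Section 9.1.1, Secondary Objective 2, item 1 sets the response: "Using difference in antibody level from Day 0 to Day 150 as the response". Two tests follow on that response.

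- For trend: "exact Jonckheere-Terpstra tests will be performed to determine if there is a dose response".
- For group differences: "exact stratified Wilcoxon rank sum tests, stratified on dose level, will be performed to determine if there are differences between the dose groups".

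The second sentence names no grouping factor other than dose.

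Two other statements in Section 9.1.1 bear on it. Under the primary objective, Day 150 concentrations are compared across doses: "A Kruskal-Wallis test will be performed to check for any significant differences in the antibody concentrations of the three dose groups", with pairwise Mann-Whitney tests if that is significant. The opening paragraph gives, as one purpose of the trial, "to compare the response by the two vaccines". Nothing else in item 1 explicitly serves that vaccine comparison.

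**The concern.** Stratifying on a factor removes that factor from the comparison. Observations are ranked against others in the same stratum only, so a shift shared by everyone at a dose level leaves the statistic unchanged. A test stratified on dose therefore carries no information on dose, which is the effect that the sentence says it will detect.

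What is at stake is the meaning of one reported p-value. If the test is run in the form that can be computed and labelled as the sentence says, a non-significant result reads as no dose difference whatever the true dose effect, and a significant one reads as a dose difference when it reflects the vaccines or their assay scales. Section 9.1 says the results will inform dosing in later trials, so the label matters. If the vaccine comparison was intended, item 1 does not state it.

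**Working it through.** The protocol gives no figure for this test, so there is none to reproduce. The check is algebra followed by simulation.

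**Inputs**
- Test, stratum and purpose: Section 9.1.1, as quoted above.
- Group size: 10 vaccinees per vaccine and dose (Sections 3.3 and 6.2). Section 9.2 plans on the same number: "a sample size of 10 volunteers per dose group would permit detection of at least a five-fold difference in antibody concentration between groups".
- Variability: Section 9.2 gives a coefficient of variation of about 1.2 to 1.4. The simulation takes the SD of ln antibody as 1.0, a lognormal CV of √(e^1.0 − 1) = 1.31.
- Significance level: 0.05, two-sided. This is an assumption here, because Section 9.1.1 states 0.05 only for the Kruskal-Wallis and Mann-Whitney family.
- Baseline antibody is taken as negligible, so the change from Day 0 ranks as the Day 150 level does.

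**Step 1: dose as both stratum and group.** The null variance of the stratified rank-sum statistic is the sum over strata of m·n·(m + n + 1)/12, where m and n are the two group sizes in the stratum. If both roles are played by dose, each stratum holds one group only, for example m = 10 and n = 0. Then m·n = 0 everywhere, the variance is 0 and there is no test.

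**Step 2: vaccine against vaccine within dose.** Here m = n = 10 in each of three strata, so the variance is 3 × (10 × 10 × 21/12) = 3 × 175 = 525 and the test exists. Rejection rates over 5,000 simulated trials, using the large-sample form of the statistic:

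| True effect | Vaccine test stratified on dose | Kruskal-Wallis across doses, one vaccine |
|---|---|---|
| None | 0.050 | 0.043 |
| Dose only, 5-fold per step | 0.051 | 1.00 |
| Dose only, 25-fold per step | 0.047 | 1.00 |
| Vaccine only, 3-fold | 0.981 | 0.048 |
| Dose 5-fold per step and vaccine 3-fold | 0.980 | 1.00 |

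The Monte Carlo standard error at 5% is √(0.05 × 0.95/5000) = 0.003, so the first three values in the middle column cannot be told apart from the nominal level.

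A second run of 4,000 trials set the dose effect from lowest to highest dose. At 1-, 5-, 25- and 100-fold the stratified test rejected in 5.3%, 5.2%, 5.0% and 5.3%. Kruskal-Wallis within one vaccine rejected in 85% at 5-fold overall. With no dose effect, a 2-fold vaccine difference gave 71% for the stratified test.

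**Step 3: a form that does test dose.** Comparing two doses with stratification on vaccine rejects in 0.054 of trials under the null, 0.906 at a 3-fold and 0.997 at a 5-fold dose difference.

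**The case against.** The strongest defence is that the sentence has a sensible reading. It speaks of dose level for the stratum and dose group for the comparison. Section 6.2 lists six groups, one per vaccine and dose. If a dose group means one such cell, each dose level contains two of them, and the test compares the vaccines within dose. The Jonckheere-Terpstra test just before it already covers dose response. This is plausible and may well be what was intended. It is not what the text says: the Kruskal-Wallis sentence in the same section uses the term for the three doses, and no other passage settles the meaning.

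It can also be said that an analyst who codes vaccine as the group would know what is being compared, so mislabelling is not inevitable. That is fair. The risk arises only if the result is reported under the stated label.

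A reader might infer more than the documents support:

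- *That the trial cannot answer its dose question.* It can. Jonckheere-Terpstra uses the same response, Kruskal-Wallis and Mann-Whitney cover Day 150, and the longitudinal model explores dose effects.
- *That vaccine is the only factor available within a dose level.* Each cohort also has 2 placebo recipients (Section 3.3). Active against placebo, 10 against 2 in three strata for one vaccine, can reach an exact two-sided p of 2/66³ = 2/287,496, about 0.000007. That contrast does not isolate dose either, but it shows that the flat 5% belongs to the vaccine reading.
- *That the two ELISAs are on different scales.* Section 6.8.1 reads concentrations "by comparison to a standard curve generated with known positive control sera included on each ELISA plate" and does not say whether the anti-Pfs25 and anti-Pvs25 scales share a unit. Silence in a brief assay summary is not evidence that they differ. It is a condition on interpreting a vaccine comparison.

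Deferral of detail to an analytic plan does not remove the point, because the protocol itself fixes the test, the stratum and the purpose, and these do not fit together.

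**Conclusion.** The point holds for this one test. As worded it is undefined. In its vaccine-against-vaccine form it has no power for dose: rejection stays at about 5% from no dose effect up to 25-fold per step, while a 3-fold vaccine difference alone is detected in 98% of trials.

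The undefined case, and the cancelling of a shift common to both vaccines at a dose level, follow from the structure of the test and need no distributional assumption. The percentages for vaccine and Kruskal-Wallis effects assume lognormal antibody levels with SD 1.0 on the ln scale, 10 per cell, negligible baseline and two-sided 0.05.

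The consequence is limited to a secondary analysis and the label on its result. The sample size statement and the stopping criteria do not use this test. That the vaccines were meant is an inference, and the sponsor should state the intended comparison.

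**What to change.** Rewrite the sentence in Section 9.1.1, Secondary Objective 2, item 1, so that the comparison is named and the test matches it.

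- **If the two vaccines are meant:** say that the test looks for differences between the two vaccines. Keep the stratification on dose level and the Day 0 to Day 150 response. Add that the result is interpreted only if the anti-Pfs25 and anti-Pvs25 ELISA scales are comparable.
- **If the doses are meant:** drop the stratification on dose and compare doses within each vaccine, or compare doses with stratification on vaccine.

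Carry the same wording into the analytic plan. The cost is one or two sentences, with no new data, visits or assays.
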